## Abstract

**Introduction:**

Myelomeningocele is a severe type of spina bifida, resulting from improper closure of the neural tube. This condition drastically affects the structures of the spinal cord resulting in deficiencies. The combination of these deficiencies results in an overall decrease in mobility and functional participation amongst this population. Physiotherapy plays an essential role in rehabilitating people with MMC. The current literature shows that resources such as photobiomodulation (PBM) may support the rehabilitation of neurological conditions. The aim of the proposed study is to evaluate the effects of photobiomodulation (PBM) combined with physical therapy on functional performance in children with low lumbosacral myelomeningocele.

**Materials and methods:**

This is a protocol randomized clinical blind study, that will include 30 individuals of both sexes, aged between 5 to 8 years, diagnosed with low and sacral lumbar myelomeningocele and capable of performing the sit-to-stand task. The participants will be randomly assigned into two treatment groups: PBM + physiotherapeutic exercises and sham PBM + physiotherapeutic exercises. Irradiation will be carried out with light emitting diode (LED) at a wavelength of 850 nm, energy of 25 J per point, 50 seconds per point and a power of 200 mW. The same device will be used in the placebo group but will not emit light. Muscle activity will be assessed using a portable electromyograph (BTS Engineering) and the sit-to-stand task will be performed as a measure of functioning. Electrodes will be positioned on the lateral gastrocnemius, tibialis anterior and rectus femoris muscles. The Pediatric Evaluation of Disability Inventory will be used to assess functional independence. Quality of life will be assessed using the Child Health Questionnaire—Parent Form 50. Changes in participation will be assessed using the Participation and Environment Measure for Children and Youth. The data will be analyzed with the aid of GraphPad PRISM.

**Discussion:**

The results of this study can contribute to a better understanding of the effectiveness of PBM on functioning and quality of life in children with myelomeningocele.

**Clinical trial registration:**

**ClinicalTrials.gov Identifier**: NCT04425330.

## Introduction

Myelomeningocele (MMC) is a severe type of spina bifida resulting from the improper closure of the neural tube [1]. The multifactor etiology involves environmental and maternal factors. This condition drastically affects the structures of the spinal cord, which can result in paraplegia, skeletal deformities, muscle weakness, the loss of sensation, impaired coordination, impaired balance, hydrocephalus, Arnold Chiari malformation, and defecatory, urinary and sexual dysfunctions, reducing the mobility and functionality of these individuals [2]. After an injury to the central nervous system (CNS), most axons do not recover due to regenerative failure, which usually results in permanent disability [3]. The aim of treatment strategies for this condition is to minimize the extent of the defect by reducing possible sequelae. Classic treatment for MMC consists of surgical closure of the MMC defect in the intrauterine phase or shortly following birth [3].

Physiotherapeutic interventions focus on the optimization of mobility and maximization of independence and participation, which can be facilitated by muscle strengthening, adaptive positioning and better postural control. However, evidence on the effectiveness of physiotherapeutic exercises in children with MMC is limited [4].

The current literature describes resources that use light as a therapeutic means to assist in the rehabilitation of patients with neurological conditions, such as stroke, neurodegenerative diseases and spinal cord injuries [5]. Photobiomodulation (PBM) is the application of a low intensity light (red and infrared light), such as low-level laser or a light emitting diode (LED), to biological tissues [6,7]. Both laser and LED have monochromatic radiation, although LED has a larger spectral width. Furthermore, Laser waves have organization favoring greater collimation, whereas LED waves are incoherent and the light is therefore not collimated, which enables treating larger areas. Despite some differences in the mode of functioning, both devices are efficient for PBM and LED has the advantage of being more affordable [8,9].

The therapeutic effect of phototherapy is achieved through the application of monochromatic or narrow-band light in tissues. PBM influences cell activity through the stimulation or inhibition of chemical and physiological functions [5]. The magnitude of the effect of PBM is influenced by the wavelength, energy density (fluence), power density, type of injury and absorption spectrum of the photoreceptor. Photons stimulate chemical changes in the interior of the cell, causing biological reactions, triggering neuroprotective responses, improving metabolism and blood flow as well as diminishing inflammatory processes and oxidative stress. As a result of these benefits, PBM has been widely used as an adjuvant in the treatment of numerous diseases [5,10,11].

Studies involving an experimental model of spinal cord injury have demonstrated that both the red and infrared wavelengths have the potential to be an effective, non-invasive means of therapy, promoting axonal sprouting, an increased concentration of glial cells and nerve connections as well as improvements in function and sensitivity [12,13]. In a clinical trial involving individuals with spinal cord injuries, PBM exerted positive effects on motor function, especially during isotonic contraction of the stimulated muscles, which were assessed using electromyography (EMG) [14]. Thus, the combination of physical therapy and PBM is promising treatment for individuals with MMC.

Therefore, the aim of the proposed study is to evaluate the effects of photobiomodulation combined with physical therapy on the functional performance of children with low lumbosacral myelomeningocele. We hypothesise that a photobiomodulation combined with physical therapy may enhance functional performance and health-related quality of life of children with MMC.

## Materials and methods

Invitations to participate in the study will be made after the determination of patients undergoing physical therapy or on the waiting list of the Integrated Health Clinic of Nove de Julho University. The study will obey the norms governing research involving human subjects (Resolutions 466/12 and 510/2016 of the Brazilian National Board of Health) following approval from the Human Research Ethics Committee of Nove de Julho University (certificate number: 4.308.134). The protocol will be in accordance with the SPIRIT statement. The participants or their guardians will sign a statement of informed consent agreeing to participate in the study. Clinical trial registry: Trials (ClinicalTrials.gov Identifier: NCT04425330).

### Participants

Eligibility for participation in the study will depend on the following criteria:

Inclusion criteria: Individuals of both sexes, aged between 5 to 8 years, diagnosed with low and sacral lumbar myelomeningocele and capable of performing the sit-to-stand task (transferring from a sitting position to a standing position).

Exclusion criteria: Cognitive impairment that compromises the ability to communicate and answer the questions that will be posed; neuromuscular scoliosis; subluxation or luxation of the hip or knee; other disease of the central nervous system.

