### Randomization

Participants will be assigned to a treatment group through a web-based randomization service (randomization.com) by an independent assessor, who, apart from generating the randomization sequence, is neither involved in the research process nor with participants. Both participants and main researchers will be masked to the randomization sequence throughout the whole study period. Participants will be randomized and assigned in two groups: Group 1 will be submitted to physiotherapeutic exercises and active PBM (n = 15). Group 2 will be submitted to physiotherapeutic exercises and sham PBM (n = 15).

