#### Calculation of sample size and statistical analysis

The sample size was calculated using the G * Power software (version 3.1.9.2) based on our previous pilot study (F test, repeated-measures ANOVA, intra-between interactions). Considering an effect size of 0.58 for the primary outcome (functional skills) and assuming a possible 10% dropout rate, a total of 30 patients (15 in each group) will be required to reach a 5% significance level with a 90% power. Descriptive statistics will be performed to determine the normality of the data and the mean change (standard deviation, 95% confidence interval) in each group will be calculated. GraphPad PRISM version 7.0 (GraphPad Software—San Diego, CA, USA) will be used for all analyses. A mixed factor ANOVA model will be employed to compare the effects of the interventions in each group in terms of functional variables (PEDI and EMG), quality of life questionnaire and social participation over time (pre-treatment, post-treatment and 30-day follow-up). A 95% confidence interval will be used to establish any differences and a p-value <0.05 will be indicative of a statistically significant difference between groups (two-tailed). If the supposition of normality is not met, pairwise comparisons between groups will be performed using a nonparametric test, as appropriate, for independent samples (Mann-Whitney U test) or dependent samples (Wilcoxon test). The alpha level will be adjusted to 0.0033 (Bonferroni correction) to avoid a type 1 error.

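### Lesion level is known at entry, yet neither the allocation described nor the stated model uses it; with 15 children per arm it could cheaply enter both

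*Protocol article*

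**What the plan says.** **Eligibility.** The Participants section admits children "aged between 5 to 8 years, diagnosed with low and sacral lumbar myelomeningocele" who are also "capable of performing the sit-to-stand task (transferring from a sitting position to a standing position". I read the diagnosis as covering two neurological levels, low lumbar and sacral. The aim in the Introduction treats them as one population: "functional performance of children with low lumbosacral myelomeningocele".

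**Allocation.** Under Randomization, "Participants will be assigned to a treatment group through a web-based randomization service (randomization.com) by an independent assessor", and "Participants will be randomized and assigned in two groups" of 15 each. No stratification, blocking or minimisation factor is named.

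**Analysis.** The sample size and statistical analysis section states: "A mixed factor ANOVA model will be employed to compare the effects of the interventions in each group", with repeated measurement "over time (pre-treatment, post-treatment and 30-day follow-up". The only factors named are group and time. If normality fails, the fallback is Mann-Whitney or Wilcoxon tests.

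**The concern.** Lesion level follows from the eligibility diagnosis, so it is available before randomisation at no cost. It could plausibly influence how much function a child gains during the trial. The Introduction itself lists type of injury among the things that influence the size of the photobiomodulation (PBM) effect, although that is only weak support for a difference between these two levels.

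With 15 per arm, simple randomisation often leaves the arms unequal on a two-level factor. Comparing change removes a difference in starting score, but not a difference in rate of gain. If one level gains faster and one arm happens to hold more of those children, the excess appears in the group-by-time contrast, where it can add to or hide a PBM effect. Any variance of change that lesion level explains also stays in the error term.

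**Working it through.** The plan gives no figure on lesion level to reproduce. I use only its 30 children and 15 per arm. The lesion split and the lesion effect on change are not in the documents and are assumed.

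**1. How often the arms differ by chance.** Suppose 15 children have each level, and let X be the number of sacral lesions in the PBM arm. Then P(X = x) = C(15,x)·C(15,15−x)/C(30,15), and the gap between arms is |2X − 15|, always odd.
- Gap of 1 (X = 7 or 8): 2 × 6435² / 155117520 = 0.534
- Gap of 3 or more: 1 − 0.534 = **0.466**
- Gap of 3 exactly (X = 6 or 9): 2 × 5005² / 155117520 = 0.323
- Gap of 5 or more: 0.466 − 0.323 = **0.143**

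With other splits (6, 8, 10 or 12 children in the smaller stratum) the gap is even, so 3 or more means 4 or more. The probabilities are 0.17, 0.21, 0.25 and 0.26.

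**2. What a gap does to the estimate.** Shift = (gap/15) × lesion difference in mean change. For an assumed difference of 0.5 to 1 SD:
- Gap of 3: 0.20 × (0.5 to 1) = 0.10 to 0.20 SD
- Gap of 5: 0.33 × (0.5 to 1) = 0.17 to 0.33 SD

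The shift is conditional on the allocation obtained and can go either way.

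**3. Validity of the planned comparison.** I simulated change-score analyses with 8,000 runs per scenario, lesion prevalence 0.4 and within-child correlation 0.7 (all assumed). Overall type I error was 0.048 to 0.056.
- *Lesion and age affect level only.* The SE of the treatment effect was 0.281 unadjusted and 0.276 with baseline, lesion level and age in the model.
- *They also affect change (0.5 SD for lesion, 0.25 SD per SD of age).* The SE was about 0.31 against about 0.275. Among runs with a lesion gap of 4 or more, type I error was 0.077 unadjusted and 0.041 adjusted.

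**4. Price of adjusting under simple randomisation.** With q covariates at N = 30, the variance of the treatment effect is multiplied by about (1 − R²) × [1 + q/(27 − q)], where R² is the share of the variance of change explained.
- Lesion level and age (q = 2): factor 1 + 2/25 = 1.08; break-even R² = 1 − 1/1.08 = 7.4%
- Lesion level alone (q = 1): factor 1 + 1/26 = 1.038; break-even R² = 1 − 1/1.038 = 3.7%

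For scale, with a 50:50 split a lesion difference of δ residual SDs gives R² = (δ²/4)/(1 + δ²/4): 5.9% at δ = 0.5 and 20% at δ = 1.

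**5. Stratifying on lesion level and keeping it in the model.** Two simulations were set so that the planned comparison has about 90% power when nothing else matters. The second used 30 children, 15 of each level, a treatment difference of 1.226 residual SDs (90% power for a two-sample t test) and 20,000 runs.

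| Assumed effect on change | Planned analysis | Stratified, lesion in model |
|---|---|---|
| None | 0.898; 0.905 | 0.900; 0.896 |
| Lesion 0.5 SD | second run only: 0.879 | 0.896 |
| Lesion 1 SD, age 0.25 SD | 0.813; 0.805 | 0.877; 0.881 |

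With no effect of either factor, adding both covariates under simple randomisation lowered power to 0.865 and 0.879. In the second run, stratifying without the model term made the test conservative: type I error was 0.032 with a 1 SD lesion effect. The two changes therefore belong together.

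**The case against.** The strongest reply is that nothing here is an error. Unadjusted analysis of a simply randomised trial is valid, and its standard error already allows for chance imbalance. Baseline is a level of the time factor, so stable differences drop out of the interaction. Eligibility already narrows the population: lower lesions only, ages 5 to 8, able to stand from sitting, with scoliosis, hip or knee luxation and other central nervous system disease excluded. The text does not say that the list is unstratified, and a condensed article may leave strata or covariates to a fuller document.

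Most of this stands. It rules out three stronger readings that a reader might infer:
- **That the planned test is biased or leaves all imbalance uncorrected.** Step 3 contradicts this. Only an effect on rate of gain is at issue, and only conditionally on the allocation obtained.
- **That the plan demonstrably wastes precision.** The documents give no lesion effect on change, so a loss is possible but not shown.
- **That age must be adjusted for because the primary score is a raw count.** The Functional skills section describes a sum of items but also defers scoring to the manual, so lack of age standardisation is not established. Adding age as well can lose power (step 4).

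What the reply does not remove is the practical point. The article fixes the model, its time levels, the software and the fallback tests without lesion level, and using a factor already in hand costs almost nothing.

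**Conclusion.** The point holds as a modest improvement in design and analysis, not as an error that invalidates the trial. The method described does not use lesion level. A gap of 3 or more children between arms is close to an even chance (47%) and a gap of 5 or more about one in seven (14%) if the levels split evenly; for the uneven splits examined, a gap of 4 or more has probability 0.17 to 0.26.

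Whether the gap matters depends on an unknown, the effect of lesion level on change. With no effect, stratifying and modelling changes power by under one percentage point. With an assumed 0.5 SD effect it gains about 2 points (0.879 to 0.896). With 1 SD, plus a small age effect, it gains about 6 to 8 points (0.813 to 0.877; 0.805 to 0.881). The case therefore rests on small cost and plausible benefit. Age adjustment is optional.

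**What to change.** **Randomization section.** Have the independent assessor generate the list separately for low lumbar and sacral lesions, in permuted blocks of concealed and varying size. Concealment matters because, under Blinding, a separate therapist delivers the active or sham irradiation, and small fixed blocks would make later assignments easier to predict.

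**Statistical analysis section.** Include lesion level as a prespecified term in the analysis of change, and confirm that the named software can fit it. The Mann-Whitney fallback takes no covariate, so say how lesion level is handled if that test is used.

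**If allocation has begun.** Leave the list alone and prespecify only the lesion-level term before unblinding. Under simple randomisation the term pays if lesion level explains more than about 4% of the variance of change. Below that it costs up to about 4% in variance.

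**If strata or covariates are already set in a fuller document,** one sentence saying so settles the point.

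**Cost.** No new data, provided lesion level is recorded for each child. A two-visit change analysis loses about one error degree of freedom (28 to 27). A lesion-by-time term over three visits uses two within-subject degrees of freedom plus one between subjects. Incomplete blocks may move the arms slightly off 15:15. Age can be added, but lesion level and age together under simple randomisation pay only above about 7% of the variance of change.

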### Randomization

Participants will be assigned to a treatment group through a web-based randomization service (randomization.com) by an independent assessor, who, apart from generating the randomization sequence, is neither involved in the research process nor with participants. Both participants and main researchers will be masked to the randomization sequence throughout the whole study period. Participants will be randomized and assigned in two groups: Group 1 will be submitted to physiotherapeutic exercises and active PBM (n = 15). Group 2 will be submitted to physiotherapeutic exercises and sham PBM (n = 15).

### Blinding

The participants will be unaware of whether they are in the active or sham PBM group.The evaluator and researcher in charge of the exercises will be unaware of the allocation of the participants to the different groups.A therapist who will not participate in the evaluations or physical therapy sessions will administer the photobiomodulation.

### Interventions

#### Photobiomodulation protocol

For irradiation, the subjects will be positioned comfortably in the prone position on an examining table. To determine the irradiation site, palpation will be performed of the spinous processes for the localization of the defect. The location with the absence of a spinous process will be considered the defect site. The location with the absence of a spinous process will be considered the defect site, to which four points will be irradiated in sequence under the injury level (Fig 1).

**Fig 1 pone.0253963.g001:**
[figure not shown]
Participant positioning for irradiation.

The irradiation will be carried out twice a week for 3 minutes and 20 seconds in a total of 24 sessions with LED (Table 1).

**Table 1 pone.0253963.t001:** Photobiomodulation.

Parameter	
Center wavelength [nm]	850
Spectral bandwidth (FWHM) [nm]	20
Operating mode	Continuous wave
Average radiant power [mW]	500
Polarization	Random
Aperture diameter [cm]	1.9
Irradiance at aperture [mW/cm^2^]	176
Beam profile	Multimode
Beam spot size at target [cm^2^]	2.84
Irradiance at target [mW/cm^2^]	176
Exposure duration per site [s]	50
Radiant exposure [J/cm^2^]	9
Radiant energy per site [J]	25
Number of sites irradiated	4
Radiant energy per session [J]	100
Area irradiated per session [cm^2^]	11.34
Application technique	Contact
Number of treatment sessions	24
Frequency of treatment sessions	2x per week
Total radiant energy [J]	2400

nm = nanometer; J = joules; s = seconds; mW = miliwatts.

#### Physiotherapy

One of the characteristics of the physical therapy program is the practice of functional activities through repeated active, self-generated movements, which will be directly linked to the fulfillment of a goal defined by the child and/or family, such as walking without assistance during recess at school. Thus, the exercises will be individualized and personalized for each child [15].

Physiotherapy will be performed with the aim of minimizing disabilities and accelerating functional independence. According to Luft [16], it is necessary to establish the intensity, motivation and training elements in order for new motor representations and new sensory and motor connections to occur.

Intensity: The participants in both groups will undergo the exercise program for 45 to 60 minutes in two sessions per week for 12 consecutive weeks.Motivation: All exercises will be associated with playful activities, such as ball playing, fishing, etc. The participants may also be take part in a story of princesses and superheroes that enable them to perform the tasks related to the goals [17].Training elements:

The exercises will be performed through the practice of functional training. (Fig 2) Five repetitions of each transition will be performed in each session. The participants will perform strengthening exercise of the lower limb muscles such as knee flexors and extensors and hip adductors and abductors (10 to 20 repetitions). Strengthening the trunk muscles will be performed through functional movements, such as transferring from the lying to sitting position, along with the aid of balls and rolls, including five repetitions in every session. The exercises will be performed with repetitions to promote motor learning as well as improve strength and endurance [4,18,19]. During each session, the participants will be given rest interval between sets.

**Fig 2 pone.0253963.g002:**
[figure not shown]
Functional training.

#### Criteria for discontinuing intervention

Patients who fail to attend two consecutive sessions or three non-consecutive sessions will discontinue the intervention.

Materials used: Wedges, rolls, medicine balls, steps, balance bean, ankle weights (0.5–1.0 kg), cones, parallel bar, stools of different sizes, mats with different textures, trampoline, walkers.

#### Adherence

All interventions will be carried out individually. To ensure adherence to the predefined protocol, the physiotherapists will be instructed by the main investigator on how to perform the interventions and will receive exercise guidelines. The therapists will record details of the training in terms of the type and execution of exercises, level of intensity and repetitions. The physiotherapist in charge of the intervention at the participating physical therapy clinic will record symptoms of possible adverse events related to treatment. Any adverse events will be reported to the main investigator, who will then report to the regional ethics committee.

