### Outcome measures

Evaluations will be performed prior to therapy (pre-intervention [T0]), after 24 sessions of PBM + physical therapy (post-intervention [T1]) and 30 days after the completion of the intervention (follow-up [T2]) (Fig 3).

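### Adverse-event recording is qualified by relatedness to treatment at the point of capture, while the next sentence reports any event; the two should be reconciled so that all events are recorded in both arms through T2

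*Protocol article*

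**What the plan says.** The only safety procedure in the protocol article is in the Adherence section, under Interventions. It has two parts.

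- **Recording.** "The physiotherapist in charge of the intervention at the participating physical therapy clinic" is the named recorder, and that person "will record symptoms of possible adverse events related to treatment".
- **Reporting.** The following sentence reads: "Any adverse events will be reported to the main investigator, who will then report to the regional ethics committee".

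Three other sections bear on it.

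- **Physiotherapy** sets the exercise programme "for 45 to 60 minutes in two sessions per week for 12 consecutive weeks", and **Outcome measures** places the T2 evaluation 30 days after the intervention ends.
- **Blinding** says "The evaluator and researcher in charge of the exercises will be unaware of the allocation of the participants to the different groups". A separate therapist, who takes no part in evaluations or exercise sessions, gives the photobiomodulation (PBM).
- **Criteria for discontinuing intervention** says "Patients who fail to attend two consecutive sessions or three non-consecutive sessions will discontinue the intervention".

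**The concern.** In a sham-controlled trial, randomisation shows whether the light causes events. That works best when events are collected without regard to cause and counted by arm. If someone decides at the moment of capture whether a symptom is related to treatment, that judgement replaces part of the randomised comparison. An effect that nobody expects is the kind most likely to be set aside as unrelated, and if it is not written down, a later imbalance between arms cannot show it.

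The setting makes this worth attention. The participants are children aged 5 to 8, PBM is being added to their physiotherapy, and the closing section of the article expects the findings to guide clinical decisions. A safety record that looks cleaner than it is would carry into that guidance. The primary efficacy analysis is not affected.

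**Working it through.** The plan gives no figure to reproduce on this point. The main check is a comparison of the text; the arithmetic gives context only.

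**1. Recording against reporting.** The recording sentence carries a qualifier (related to treatment). The reporting sentence carries none. Reporting depends on what has been recorded or otherwise noticed. If the qualifier is applied, the set that reaches the main investigator is smaller than the set the second sentence describes. If it is not meant to be applied, the first sentence says something unintended. Either way the two sentences do not state the same rule.

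**2. Who judges relatedness.** The Adherence section names the physiotherapist in charge of the intervention; the Blinding section separates the exercise researcher (blinded) from the PBM therapist. The article does not say which of them is the recorder. If it is the exercise physiotherapist, relatedness is judged without knowing whether light was given. That guards against differential recording but makes the judgement a poor filter. If it is the PBM therapist, the recorder may know the allocation (an assumption, depending on how the sham is set). Neither reading supports filtering at capture.

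**3. Scheduled contact with the recorder.** 24 sessions at 2 per week take 12 weeks, or 12 × 7 = 84 days. T2 follows 30 days later, so the period is 84 + 30 = 114 days. The share after the last scheduled session is 30/114 = 26%.

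**4. What 15 children per arm can show.** Event rates here are assumptions; the article gives none.

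- Upper limit after zero events in one arm (one-sided 95%): 1 − 0.05^(1/15) = 18%.
- Chance of at least one event in an arm, 1 − (1 − p)^15:

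| Assumed true rate p | Chance of at least one event in 15 |
|---|---|
| 5% | 54% |
| 10% | 79% |
| 20% | 96% |

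- Power to detect a difference (two-sided 5%, normal approximation, rough at this size), with p̄ the mean of p1 and p2 and n = 15: Φ{(|p1 − p2| − 1.96·√[2p̄(1 − p̄)/n]) / √[(p1(1 − p1) + p2(1 − p2))/n]}.
  - 10% v 30%: (0.20 − 1.96 × 0.146)/0.141 = −0.61, power about 27%.
  - 10% v 50%: (0.40 − 1.96 × 0.167)/0.151 = 0.48, power about 68%.
- Weight of one unrecorded event: 1/15 = 6.7 percentage points of an arm's observed proportion.

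A formal safety comparison would therefore be weak even with complete recording. With so few children, each event left out also changes the descriptive picture noticeably.

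**The case against.** The strongest reply is that the text is looser than the concern makes it. It does not say that related symptoms are the sole thing recorded, the word possible points to a low threshold, and the next sentence covers any adverse event without restriction. This is also a journal article: event definitions, the collection window and the handling of children who stop are commonly left to the full protocol. Much of this stands. Silence on those matters is not held against the plan. What remains is a qualifier that the article does state and that does not fit the sentence after it.

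A reader might go further in four ways that the documents do not support.

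- **That events between sessions, after stopping or before T2 are lost.** Nothing confines recording to what happens in a session or ends it at the last one. A parent can mention an event at the next visit, and T1 and T2 are scheduled contacts. The 26% is time without a treatment session, not time shown to lack safety collection.
- **That a child stopped for absence leaves safety follow-up.** The rule ends the intervention, not the study, and the article states an intention-to-treat analysis, which is consistent with continued evaluation.
- **That the arms cannot be compared for safety.** One recording rule covers both arms and the participants are blinded, so recorded events can be compared, if incompletely. The main limit on precision is the 15 children per arm.
- **That the attendance rule measures missed events.** Any percentage from it would rest on an assumed absence rate and on independence between sessions, and would count children stopped, not events unrecorded.

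**Conclusion.** The point holds in a limited form. The Adherence section states a recording rule qualified by relatedness, gives it to a physiotherapist whose scheduled contact ends at the last session, and follows it with a wider reporting rule. Read as written, events not suspected to be related may go unrecorded, and the sham-controlled comparison of events would then be incomplete.

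The number of events affected cannot be estimated from the document. The conclusion assumes that the qualifier would be applied literally; if staff record everything regardless, the defect is one of wording. It is a cheap improvement worth making, and not a threat to the efficacy result.

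**What to change.** Reconcile the two sentences in the Adherence section with one rule:

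- All adverse events, whatever the presumed cause, are recorded in both arms from the first session to T2.
- One open question is put to the parent at each session and at T1 and T2. Children who have stopped the intervention are asked at their scheduled evaluations.
- Relatedness is judged afterwards, in a separate field, by someone blinded to allocation.
- Health-related reasons for missed sessions are logged as events.
- Counts are reported by arm.

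The same edit should say which physiotherapist does the recording.

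The cost is one question at contacts that already take place, a short form, a change of protocol wording, and slightly more logging of trivial events. No treatment, schedule or attendance rule changes.
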